## **OBJECTIVES**

Although the long term objective of this line of research will address the underlying mechanisms of acute exercise effects on motor learning and possible brain activity changes with developmental coordination disorder (DCD), we currently defined the specific objectives of this project as follows:

- O1. To study the acute intense exercise effects on the motor learning (adaptation and consolidation) in children with and without DCD from a behavioral perspective (performance and execution).
  - O1.1- Characterize the possible motor learning modulators (physical fitness; physical activity level; attentional and cognitive capabilities) in children with and without DCD.
  - O1.2- Compare the motor learning (adaptation and consolidation) ability of children with and without DCD while performing a rotational visuo-motor task (rVMA) (CON-DCD vs. CON-TD).
  - O1.3- Examine the effect of acute intense exercise on motor learning (adaptation and consolidation) while performing a rotational visuo-motor task in children with and without DCD.
- O2. To explore cortical activation in the visuomotor integration and the attentional network areas while learning a motor adaptation task in children with and without DCD under rest or post-exercise conditions. Visuomotor integration and attentional network areas will include dorsolateral pre-frontal cortex (DLPFC), ventrolateral pre-frontal cortex (VLPFC), and oculo pre-frontal cortex (OPFC).
  - O2.1- Assess changes in cortical activation ([O2Hb]) during rVMA learning (adaptation and consolidation) in children typically developed and in children with DCD.
  - O2.2- Evaluate the impact of acute intense exercise on changes in cortical activation ([O2Hb]) during rVMA learning (adaptation and consolidation) in children typically developed and in children with DCD.
  - O2.3- Associate the presence of changes in the cortical activation variables with differences shown in behavioral variables.
- O3: To explore via a pilot study the combined use of two optical neuroimaging techniques (fNIRS and fDCS) to measure cortical activation in the visuomotor integration and the attentional network areas while learning a motor adaptation task in children with and without DCD under rest or post-exercise conditions.
  - O3.1- Evaluate the usability of the hybrid device
  - O3.2- Assess the potential to obtain new relevant information of the hybrid device in comparison with using on technology (fNIRS or fDCS) alone.

## **METHOD**

### **Participants**

A total of 120 participants divided into two cohorts (60 children with DCD and 60 TD children) will be recruited for the study. Taken into consideration a 5-6% prevalence for DCD in the children population (Blank et al., 2012; Harris, Mickelson, & Zwicker, 2015; Kadejso & Gillberg, 1999; Lingam et al., 2009; Tsiotra et al., 2006; Zwicker et al., 2012), screening a total amount of 1000 children (from 6-8 schools, see Annex 2) using a motor-based questionnaire completed by parents and by teachers (M-ABC2 checklist, Henderson, Sugden, & Barnett, 2007) will be a first step to identify the necessary children with DCD on the basis of their difficulties in daily living activities and academic performance. Those children early identified as DCD by the motor-based questionnaire will be then evaluated to confirm their inclusion in the DCD group. Children in the DCD group will be selected based on the following inclusion criteria: (1) a movement assessment battery for children – second edition (MABC-2, Henderson et al., 2007) score of <15% administered by trained testers. The MABC-2 is a standardized and normative referenced test that is designed to identify motor impairment in children aged 3-16 years by evaluating manual dexterity, ball skills, and static and dynamic balance. Because DCD children present motor performance substantially below that expected given the person's chronological age and intelligence, a <15% cut-off is usually used to indicate children with probable DCD (Blank et al., 2012; Gueze et al., 2001). The Spanish translated edition and norm-referenced in Spain MABC-2 (Ruiz & Graupera-Sanz, 2012) will be used for scoring. (2) An average or better cognitive ability tested through the Test of Nonverbal Intelligence version 4 (TONI-4) and scoring above 85 in the intellectual quotient (IQ). (3) A parent-report history to confirm that motor difficulties showed by their child cannot be explained by any other neurological, developmental, and /or severe psychosocial problem according to the child's pediatrician. Comorbid attention deficit hyperactivity disorder, attention deficit disorder, and dyslexia will be acceptable in order to better represent the DCD population since data population-based studies suggest that almost 40% of the children with DCD have combined problems related to learning and/or attentional disorders (Blank et al., 2012; Harris et al., 2015).

## Experimental protocol

Participants will engage in five different sessions (see Figure 3). Before enrolling in any of the study sessions, participants along with their guardians will complete a set of questionnaires to assess (Annex 5): (1) the participant health status to participate in physical activity (Physical Activity Readiness Questionnaire, PAR-Q); (2) the participant's physical-activity engagement (Spanish version of the Physical Activity Questionnaire for Children, PAQ-C, validated by Benítez-Porres et al., 2016); (3) the participant's academic performance and difficulties performing daily living activities (Spanish version of the M-ABC2 checklist, validated by Ruiz & Graupera-Sanz, 2012); (4) the possible comorbidities permitted in this study such as attention deficit hyperactivity disorder, attention deficit disorder, and/or dyslexia; (5) the type and dose of medication a child currently takes; (6) possible psychosocial problems assessed by the Conners Comprehensive Behavior Rating Scales (Conners CBRS; Conners, 2008); (7) the exclusion criteria via a checklist; and (8) the family history about DCD, neurological disorders or mental health, and family's socio-economic status (SES) and parental education. At the same time, the participant's teacher will also complete the M-ABC2 checklist (Ruiz & Graupera-Sanz, 2012) questionnaire to identify motor coordination problems and the participant's academic

level. Participant handedness will be determined based on their preferred hand for everyday activities and confirmed by the M-ABC criteria.

In the first session, participants' intelligence level will be assessed through the TONI-4 while their motor development will be evaluated by the MABC-2. Basic anthropometric parameters (height and body mass) will be also obtained and used to calculate body mass index (BMI). The fitness level (estimated  $\text{VO}_2\text{max}$ ) will be assessed through the 20-meter shuttle run test (20mSRT) (Léger, Mercier, Gadoury, & Lambert, 1988). The 20mSRT start at one longitudinal end of the zone limited by 20 m long and 1.5 m wide, and move back and forth following the rhythm of an audio track. Participants must match the arrival at each end of the bounded zone (stepping the line) with an auditory signal (beep). The initial speed is 8.5 km/h but the frequency of the beep increase every minute (stage) leading the participants to increase their speed 0.5 Km/h. The test ends when the subjects abandon or fail to maintain the rhythm for 2 consecutive lines. To encourage participants' performance during the fitness test and the intense exercise (iE) bout, for each 20 m back and forth ran they will receive card containing cartoon-character pictures that would be used in the third session of the study to perform a memory game of pairing two equal cards, so the more cards collected the better. To further support children, an adult will run next to the child to assist in keeping the pace and provide encouragement. The last completed stage (Emax) of the test will be recorded. In addition, during the 20mSRT, beat-by-beat values for the RR intervals (time between peak values in an electrocardiogram) will be registered using a Polar RS800CX (Polar Electro) at 1000 Hz frequency. The heart rate (HR) will serve as a control parameter for the intensity of the test. A minimum of 48h delay will be applied between sessions 1 and 2. Only participants that meet inclusion-exclusion criteria will be enrolled further into the study.

|           |                                            |                                          |                                          |                                          |
|-----------|--------------------------------------------|------------------------------------------|------------------------------------------|------------------------------------------|
| Session 1 | Intelligent level test (TONI-4)            |                                          |                                          |                                          |
|           | Basic Anthropometry (height and body mass) |                                          |                                          |                                          |
|           | Motor development/coordination (MABC-2)    |                                          |                                          |                                          |
|           | Fitness level (20mSRT)                     |                                          |                                          |                                          |
| Session 2 | Familiarization rVMA (1 x 20 trials 0°)    |                                          |                                          |                                          |
|           | Baseline rVMA (1 x 104 trials 0°)          |                                          |                                          |                                          |
|           | EX-DCD                                     | EX-TD                                    | CON-DCD                                  | CON-TD                                   |
|           | iE 13 min                                  | iE 13 min                                | Rest 13 min                              | Rest 13 min                              |
|           | Adaptation rVMA
(1 x 312 trials -60°)   | Adaptation rVMA
(1 x 312 trials -60°) | Adaptation rVMA
(1 x 312 trials -60°) | Adaptation rVMA
(1 x 312 trials -60°) |
|           | Retention rVMA 1 h (1 x 104 trials -60°)   |                                          |                                          |                                          |
|           | Retention rVMA 24 h (1 x 104 trials -60°)  |                                          |                                          |                                          |
| S4 S3     | Retention rVMA 7d (1 x 104 trials -60°)    |                                          |                                          |                                          |

Figure 4. Schematic overview of the experimental procedure.

At the start of session 2, participants will be familiarized with the rVMA protocol (familiarization set) by performing 20 trials of non-rotated ( $0^\circ$ ) practice trials. Afterwards, a non-rotated baseline condition set (104 trials) will be performed. After the baseline set, the EX groups (i.e., EX-DCD and EX-TD) will perform a 13-min iE session while the CON groups (i.e., CON-DCD and CON-TD) will rest the same period of time reading or holding a conversation, no additional exercise or musical activity will be permitted. Next, all participants will do an adaptation set (312 trials) in the rVMA task, with a clockwise rotation of  $60^\circ$  applied to the cardinal coordinates of the cursor movement. At one hour after the end of the adaptation set, all participants will perform a  $60^\circ$  clockwise retention set (short-term retention, RT1h, 104 trials). At the end of session 2, all participants will perform a memory game with the cards they collected during the 20mSRT and potentially the iE.

Sessions 3 and 4 will occur 24 h and 7 days from the end of the adaptation set. In each session, participants will perform a  $60^\circ$  clockwise rotated retention set (mid and long term retentions, RT24h, and RT7d respectively, 104 trials each).

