#### Attention: Exercise as an enhancer of learning via attention

Although the specific underlying mechanisms by which physical exercise can improve learning and memory are not clear, several proposals have been placed forward. At the molecular level, and as mentioned before, changes in the concentrations of catecholamines (e.g. norepinephrine; T. McMorris, Collard, Corbett, Dicks, & Swain, 2008) and neurotrophic factors

(e.g. brain derived neurotrophic factor, BDNF; Koehl et al., 2008; Schwarz & Kindermann, 1990; Winter et al., 2007) have been shown to be related to the enhancement of learning when exercise is implemented. Alternatively, two psycho-cognitive factors, arousal and attention, may also mediate the relationship between physical exercise and improved learning. An optimal level of arousal is necessary to effectively use the limited attention capacity (Kahneman, 1973). This effective use of attention, in turn, facilitates learning (Catroppa & Anderson, 1999).

It is, therefore, plausible that moderate acute physical exercise places the individual at the appropriate level of arousal (not too high, not too low) and assists in the maintenance of attention, so the learning and consolidation of a new motor-perceptual task, like the rVMA task, are improved. In fact, Medina et al. (2010) found that the attention deficits in children with ADHD could be minimized via physical exercise using an acute interval exercise of 30 minutes and assessing sustained attention using the Conner's Continuous Performance II test. However, these authors had no measurements of learning or memory. Furthermore, no studies have examined the effect of acute exercise on the attention capacity of children with DCD and whether sustained attention plays a role in the exercise-induced enhancement of learning.

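### Only EX children earn extra picture cards in the randomised period and carry a larger deck into the memory game, so an EX–CON difference cannot be credited to exercise alone

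*Protocol*

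**What the plan says.** All of this is in the Protocol, mainly under Experimental protocol.

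- **When cards are earned.** The session 1 text introduces them with "To encourage participants' performance during the fitness test and the intense exercise (iE) bout". They therefore belong to two runs: the 20mSRT, which every child does before randomised treatment begins, and the iE, which only EX-DCD and EX-TD do.
- **How many.** "for each 20 m back and forth ran they will receive card containing cartoon-character pictures that would be used in the third session", and "so the more cards collected the better".
- **Adult runner.** The next sentence adds that "an adult will run next to the child to assist in keeping the pace and provide encouragement".
- **Control condition.** In session 2 the CON groups "will rest the same period of time reading or holding a conversation, no additional exercise or musical activity will be permitted". No cards are described for them in that period.
- **The game.** The session 2 text says that, at the end of that session, "all participants will perform a memory game with the cards they collected during the 20mSRT and potentially the iE".
- **The claim that depends on it.** H1 predicts that the exercise bout improves consolidation, and O1.3 examines the effect of acute intense exercise. Under Statistical analysis, retention is analysed by a Group × Exercise × Time ANOVA in which Exercise is the only condition factor.
- **Mechanism offered.** The section on exercise as an enhancer of learning via attention says that "two psycho-cognitive factors, arousal and attention, may also mediate the relationship between physical exercise and improved learning".

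**The concern.** The randomised comparison is 13 minutes of shuttle running against 13 minutes of rest. Only the running arm also receives a reward tied to performance. It probably also has an adult alongside giving encouragement. Both come shortly before adaptation (the plan allows a 4-minute transition) and so precede every learning outcome. The extra cards then go into a memory game that, on the session 2 text, falls between the 1 h and 24 h retention tests. The arms thus differ in reward before learning and in the size of a memory task afterwards, as well as in exercise.

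These differences coincide exactly with arm, so no term or covariate in the planned ANOVA can separate them from exercise. The retention tests matter most here, because consolidation is where H1 predicts a benefit. The plan also gives two different sessions for the game, so the document does not settle which retention tests follow it.

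**Working it through.** **Step 1: the plan's own figure.** The iE is 3 fast series of 3 min plus 2 slow series of 2 min: 3×3 + 2×2 = 13 min. This agrees with the stated duration.

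**Step 2: card counts in one illustrative case.** The plan gives no expected last completed stage (Emax) and no eligible age range, so these are assumptions. Take age 8, Emax 4 and one card per 40 m (out and back), ignoring the warm-up and any incomplete stage.

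- Vmax = 0.5×4 + 8 = 10 km/h.
- At age 8 the plan's equation becomes VO2max = 31.025 + 3.238V − 25.984 + 1.2288V = 5.041 + 4.467V. At V = 10 it gives 49.7.
- 85% speed: (0.85×49.7 − 5.041)/4.467 = 8.33 km/h. 60% speed: (0.60×49.7 − 5.041)/4.467 = 5.55 km/h.
- iE distance: 8.33×9/60 + 5.55×4/60 = 1.25 + 0.37 = 1.62 km, or about 40 cards (EX only).
- 20mSRT distance: (8.5 + 9 + 9.5 + 10)/60 = 0.617 km, or about 15 cards (both arms).
- Deck for the game: about 55 cards in EX and 15 in CON. By distance the ratio is (617 + 1620)/617 = 3.6.

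**Step 3: range.** At age 8:

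| Emax | 20mSRT, m (cards, both arms) | iE, m (cards, EX only) | EX:CON ratio by distance |
|---|---|---|---|
| 2 | 292 (7) | 1452 (36) | 6.0 |
| 4 | 617 (15) | 1620 (40) | 3.6 |
| 6 | 975 (24) | 1787 (44) | 2.8 |

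Over ages 6 to 12 and Emax 2 to 6, the iE adds 34 to 47 cards and the ratio runs from 2.7 to 6.4. At one card per 20 m the counts double and the ratio is unchanged. Taking the iE speeds as simple percentages of Vmax gives 1507 to 1842 m, inside the same range.

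**Step 4: which outcomes each difference can reach.**

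| Difference between arms | Adaptation | RT1h | RT24h | RT7d |
|---|---|---|---|---|
| Cards (and probably encouragement) in the iE | yes | yes | yes | yes |
| Unequal game, end of session 2 | no | no | yes | yes |
| Unequal game, third session, before RT24h | no | no | yes | yes |
| Unequal game, third session, after RT24h | no | no | no | yes |

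The 20mSRT cards are common to both arms and do not confound the contrast.

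**The case against.** The strongest reply is that incentives and pacing are how children are kept at the set speeds for 13 minutes, so they are part of the bout. A randomised comparison of that bout with rest answers a legitimate question, and separating exercise from everything that accompanies it would be a different trial. This stands as far as it goes: the contrast is valid for the bout as delivered. It does not explain why deck size should depend on arm, or why the game should come before the last retention test.

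The mechanism is also not in the documents. The plan names arousal and attention as possible mediators of exercise. It says nothing about reward acting on them, and nothing suggests that a picture-pairing game alters retention of a joystick rotation. That also stands. Reward acting through those factors is plausible, but it is not shown.

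The session mismatch may be a numbering slip. The same section announces five sessions but describes four, and Data reduction places the iE in session 3. Under such numbering, the third session could be the learning session itself. The plan does not settle this. If so, the game precedes RT24h.

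A reader might also infer more than the text supports:

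- **That cards and the adult runner belong to the exercise arm only.** Both also accompany the session 1 fitness test in both arms. The adult's presence in the iE is read from the preceding sentence, which names both runs. The section on the iE itself mentions neither an adult nor cards.
- **That CON children lack adult contact.** Their "will rest the same period of time reading or holding a conversation" may already involve an adult.
- **That RT24h is exposed wherever the game is placed.** If it is played in the RT24h session after the test, only RT7d is exposed.
- **That the results are biased by a known amount or in a known direction.** The arithmetic counts cards and does not measure bias.

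**Conclusion.** The point holds as an avoidable weakness in attribution. In the randomised period only EX children earn additional cards, and by design they bring a larger deck to the game: roughly three to six times larger under the stated assumptions on Emax and card rate. The reward precedes every outcome. The game cannot affect adaptation or RT1h. It precedes RT24h and RT7d on the session 2 text. On the third-session text it precedes RT7d, and RT24h only if played first. The two statements about the session must be reconciled in any case.

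The documents do not support calling the EX–CON contrast invalid. It estimates the effect of the bout with its incentives against rest. Reading that effect as acute exercise alone, as H1 and O1.3 do, is what is weakened. Confidence is high for the unequal cards and the conflicting timing, and low for any material effect on retention scores.

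**What to change.** 1. State one time for the game in both places, and put it after RT7d in session 4. No rVMA test then follows it.
2. Use one fixed deck size for every child, whatever the number of cards collected.
3. Keep the iE cards, so that motivation to run is preserved, and give CON children the same cards on a matched schedule during the 13-minute rest.
4. If the cards stay unequal, word H1, O1.3 and the report as the effect of the exercise bout with its incentives compared with rest.

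Stating whether an adult accompanies the iE, and who talks with CON children during rest, would help interpretation. Prescribing matched adult contact is optional.

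Cost: edits to the session 1 and session 2 text and to the CON procedure, and some extra cards. No added participants, sessions or measurements are needed. Children wait until session 4 for the game. A fixed deck also means that collecting more cards no longer improves the game, so what children are told about the cards needs rewording. The change is cheap before data collection. Afterwards, analysis cannot undo the overlap with arm.

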### **The intense exercise bout (iE)**

The intense exercise (iE) bout will consist of a 13-minute 20-meter shuttle run. During this exercise bout two speeds, based on a percentage of the estimated  $VO_{2max}$ , will be combined: a fast-paced speed (fast, 85% of  $VO_{2max}$ ) and a slow-paced speed (slow, 60%  $VO_{2max}$ ). A total of 3 series of 3 min of the fast-paced speed will be carried interspersed with 2 series of 2 min of the slow-paced speed. Prior to the iE start, a warm-up protocol consisting of 2 min slow and 1 min fast will be done with the objective to familiarize participants with the iE speeds. A 5-minute rest period will be guaranteed before starting the iE. Transition time between iE and rVMA will be 4 min. Participants' heart rate will be captured following the same procedure described for the 20mSRT.

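### Control rest is timed only to the 13-minute bout, so as written exercisers have 4 to 12 minutes longer than controls between the baseline and adaptation sets

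*Protocol*

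**What the plan says.** The Experimental protocol section sets the order of session 2: familiarization (20 unrotated trials), baseline (104 unrotated trials), exercise or rest, then adaptation (312 trials rotated by 60 degrees). On the step between baseline and adaptation it says of exercisers: "After the baseline set, the EX groups (i.e., EX-DCD and EX-TD) will perform a 13-min iE session". The same sentence goes on to the control arm and claims equal time for it: "while the CON groups (i.e., CON-DCD and CON-TD) will rest the same period of time reading or holding a conversation". The schematic of the procedure in the same section shows 13 minutes of exercise against 13 minutes of rest.

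The section headed The intense exercise bout (iE) builds the 13 minutes from fast and slow running series and then places further time around them. On the warm-up: "Prior to the iE start, a warm-up protocol consisting of 2 min slow and 1 min fast will be done". On the rest and the changeover: "A 5-minute rest period will be guaranteed before starting the iE. Transition time between iE and rVMA will be 4 min".

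None of these three periods is described for controls. The text also does not say whether the warm-up and the rest come before or after the baseline set. The Participants section describes controls as resting up to the point at which they start the learning task, without a duration.

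The first retention test is tied to adaptation in every group: "At one hour after the end of the adaptation set, all participants will perform" it. The 24-hour and 7-day tests have the same anchor.

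**The concern.** A rest control is there to hold everything but exercise constant, including the time since the last task practice. Here the equal-time statement covers the bout and not the whole interval that separates the unrotated trials from the first rotated trial. A team that follows both sections literally would start adaptation later in exercisers than in controls.

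Objectives O1.3 and O2.2 read the difference between exercise and rest as the effect of exercise, through the 2 x 2 and 2 x 2 x 3 ANOVAs in the Statistical analysis section. If the interval is fixed by arm, no covariate can separate it from exercise, and a larger sample does not remove it. The measure most exposed is the initial rate of learning, which the Variables section evaluates at epoch 1, just after the interval ends. Mean adaptation error is exposed too.

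**Working it through.** **Inputs** (all from the protocol)

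- Bout: 3 series of 3 minutes fast and 2 series of 2 minutes slow (The intense exercise bout).
- Warm-up: 2 minutes slow and 1 minute fast (same section).
- Rest before the bout: 5 minutes (same section).
- Transition from bout to task: 4 minutes (same section).
- Control rest: 13 minutes (schematic; the text matches it to the bout).

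**The protocol's own figure.** Bout = 3 x 3 + 2 x 2 = 13 minutes, so the stated 13 minutes is reproduced and is the running alone. Warm-up = 2 + 1 = 3 minutes.

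**Interval from end of baseline to start of adaptation**

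| Placement of warm-up and rest | Exercisers | Gap if controls have 13 min | Gap if controls have 13 + 4 = 17 min |
|---|---|---|---|
| Both after baseline | 3 + 5 + 13 + 4 = 25 | 12 | 8 |
| Only the 5-minute rest after baseline | 5 + 13 + 4 = 22 | 9 | 5 |
| Both before baseline | 13 + 4 = 17 | 4 | 0 |

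The 30-second seated reference recording before the adaptation set is made in all participants and cancels in the gap.

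**Which row is likelier.** The Experimental protocol section opens session 2 with familiarization, follows it with baseline, and only then brings in the exercise. A warm-up tied to the start of the bout fits best after baseline, which gives 25 minutes. This is an inference. What the text fixes is 13 + 4 = 17 minutes for exercisers against 13 for controls.

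**The other placement is not neutral.** If the warm-up came before baseline, exercisers would have run, including 1 minute at the fast pace, before a baseline that is subtracted from their adaptation and retention means (Variables) and compared across the four groups (Statistical analysis).

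**Where the delay can act.** Retention at 1 hour, 24 hours and 7 days is timed from the end of adaptation in all groups, so the retention intervals are equal. The gap lies wholly before the rotated task is first met. It can reach retention only through what was learned during adaptation.

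**The case against.** The strongest reply is that parity was clearly intended. The protocol claims equal time, and the Participants section keeps controls at rest until learning starts, which need not mean stopping at 13 minutes. The section that lists the warm-up, rest and transition is about the exercise bout, so its silence on controls is not an instruction that they skip the wait. This stands as evidence of intent. It does not give controls a duration, and the only figure written for them is 13 minutes.

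A reader might infer that exercisers wait 25 minutes and controls 13, and that the whole exercise contrast is therefore confounded with delay. The documents do not support that, for these reasons:

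- The 25 minutes depends on a placement that the text does not state.
- The directional exercise predictions in H1 concern consolidation and the narrowing of the gap between cohorts, and the retention delays are equal. For adaptation, H1 cites a null exercise effect in typically developing children and makes no prediction for children with DCD.
- For the imaging outcomes, a resting reference is recorded again before the adaptation set and signals are normalized to resting values. This limits slow drift over a longer gap.
- The 3-minute warm-up is itself running at the speeds of the bout, so it is partly intervention and not pure delay.
- Familiarization and baseline together are 124 trials at one target every 2 seconds: 124 x 2 = 248 seconds, about 4.1 minutes. Even the 13-minute control rest is about three times that. Neither fatigue nor fading of the unrotated mapping over 13 against 17 to 25 minutes is quantified anywhere in the protocol.

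These points limit the possible harm. They do not make the two intervals equal.

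**Conclusion.** The equal-time statement does not hold for the interval before adaptation. As written, that interval is 17 to 25 minutes in exercisers and 13 in controls, a gap of 4 to 12 minutes. The 12-minute end assumes that the warm-up and the rest both follow baseline, which is the natural reading. If the transition is also given to controls, the gap is 0 to 8 minutes. It reaches zero only if, in addition, the warm-up and the rest both come before baseline.

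What is shown is a timing imbalance aliased with arm, not a measured bias. It could affect adaptation measures and the initial rate of learning, and retention only indirectly. The size and direction of any effect are unknown. The point should be fixed because the remedy is simple and an imbalance fixed by arm cannot be separated from exercise after data collection. It does not invalidate the exercise comparison as a whole.

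**What to change.** Reconcile the Participants section, the Experimental protocol section with its schematic, and the section on the exercise bout:

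1. State the full session 2 sequence for each arm, including where the warm-up, the rest before the bout and the transition fall relative to the baseline set.
2. Define the control period by elapsed time, so that the interval from the end of the baseline set to the start of the adaptation set is the same in both arms, with controls seated throughout.
3. Record the end-of-baseline and start-of-adaptation times for each child, so that the match can be checked and reported.

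The exercise content stays as it is. The cost is protocol wording, two logged times per child and up to about 12 more minutes of quiet sitting for each control child. No extra staff or procedure is needed.
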